## Abstract

**Background:**

One-half of patients with cancer have pain. In nearly one out of two cancer patients with pain, this was undertreated. Inadequate pain control still remains an important problem in this group of patients. Therefore, in 2008 a national, evidence-based multidisciplinary clinical practice guideline 'pain in patients with cancer' has been developed. Yet, publishing a guideline is not enough. Implementation is needed to improve pain management. An innovative implementation strategy, Short Message Service with Interactive Voice Response (SVS-IVR), has been developed and pilot tested. This study aims to evaluate on effectiveness of this strategy to improve pain reporting, pain measurement and adequate pain therapy. In addition, whether the active role of the patient and involvement of caregivers in pain management may change.

**Methods/design:**

A cluster randomised controlled trial with two arms will be performed in six oncology outpatient clinics of hospitals in the Southeastern region of the Netherlands, with three hospitals in the intervention and three in the control condition. Follow-up measurements will be conducted in all hospitals to study the long-term effect of the intervention. The intervention includes training of professionals (medical oncologists, nurses, and general practitioners) and SMS-IVR to report pain in patients with cancer to improve pain reporting by patients, pain management by medical oncologists, nurses, and general practitioners, and decrease pain intensity.

**Discussion:**

This innovative implementation strategy with technical tools and the involvement of patients, may enhance the use of the guideline 'pain in patients with cancer' for pain management. Short Message Service alerts may serve as a tool to support self-management of patients. Therefore, the SMS-IVR intervention may increase the feeling of having control over one's life.

**Trail registration:**

Netherlands Trial Register (NTR): NTR2739

## Background

Pain is a major healthcare problem for patients with cancer [1] and is one of the most frequently feared symptoms [2,3]. In 2007, in a Dutch study 64% of patients with metastatic, advanced, or terminal disease [4], 59% of those on anti-cancer treatment and 33% of patients after curative treatment experienced pain [4]. Often, pain control is inadequate [2-9]. In 2007, Deandrea *et al*. demonstrated that pain in nearly one-half patients with cancer is undertreated [10]. As illustrated by the high prevalence of pain, for most patients acceptable pain reduction has not yet been reached. Up to now, no hospital-wide intervention has yet improved the treatment of pain in general [11].

A key barrier to adequate treatment of pain is ineffective communication between patients and healthcare providers about their pain [12,13]. Patients often consider information they receive from providers to be unclear [14,15]. Generally, patients lack knowledge about pain and pain management [16,17]. Several studies show that informing and educating the patient about treatment of cancer pain reduces pain intensity [18-21].

Professionals do not ask their patients systematically about their pain [22,23]. Moreover, patients seem to be reluctant to talk about their pain or to ask for pain medication [24-26] for a variety of reasons, such as concerns about addiction, tolerance, desire to please providers, and fear that reporting pain will take the physician's time away from the treatment of their cancer [27,28].

One further aspect of underreporting pain concerns assessment and documentation. There is evidence that careful and regular, systematic assessment of pain improves the perception of physicians and nurses concerning cancer pain and enhances the quality of pain management [29,30].

Healthcare providers tend to show a lack of attention to and knowledge about pain management [29,31-33] and consequently do not always treat pain according to specific guidelines [31,32]. This has been regarded as one of the main factors causing inadequate pain relief in cancer patients [29,34,35]. For these patient- and professional-related reasons, inadequate treatment of cancer pain persists, despite decades of efforts to provide clinicians with information on analgesics and pain-relieving techniques [36-42], and despite the availability of evidence-based guidelines on cancer pain [43].

The prevailing principle for treatment of cancer pain is the World Health Organization (WHO) three-step pain ladder, published in 1986 [42]. If this guideline is well applied, it is possible to achieve adequate pain relief in 70 to 90% of cancer patients [44-47].

Based on this pain ladder, a more detailed European recommendation for the use of morphine and alternative opioids has been published by the European Association for Palliative Care (EAPC)[48]. The final version of the 'Evidence-based guidelines for the use of opioids analgesics in the treatment of cancer pain: The EAPC recommendations' is in development [49].

The Dutch guideline 'Pain in patients with cancer'[50] is one of the most recent guidelines on this topic in Europe. It combines new insights and existing knowledge derived from evidence-based medicine. All relevant professional organizations of the Netherlands as well as the patient association have been involved in the development process. In a comparative study of European guidelines on this topic with the AGREE II instrument, this Dutch guideline appeared to have followed a good development process [51]. Yet, under-treatment of cancer pain may be partly caused by a lack of implementation of these clinical practice guidelines (CPGs)[10,52-54].

The present study aims to evaluate the implementation of the Dutch guideline 'Pain in patients with cancer'[50] to improve pain reporting, pain measurement, and hence pain control in patients with cancer and pain. A randomised controlled trial (RCT) with two arms will be performed in which professionals will be trained and Short Message Service with Interactive Voice Response (SMS-IVR) will be used to monitor and report pain.

Using Short Message Service (SMS) as a reminder and as tool to collect data on pain scores is innovative and promising [55]. Mobile phones are part of daily life; in 2009, nine out of ten Dutch inhabitants used a mobile phone [56]. SMS alerts have been used for asthma management [57-59], management of irritable bowel syndrome [60,61] management of diabetic patients [61] and recurrent pain in children aged 9 to 15 [62]. These studies concluded that SMS can serve as a tool to support self-management of patients. The use of mobile phone SMS alerts in the present study may be a way to encourage patient empowerment, because the patients' role in their pain management becomes more active. Empowerment has been defined by its absence of helplessness, or the feeling of having greater control over one's life [63].

We expect that SMS-IVR will increase the percentage of patients with cancer who receive adequate pain treatment and reduce pain intensity in patients with cancer, because pain will be measured systematically. In addition, patients are expected to become less reluctant to report pain and physicians will ask patient more frequently about pain.

The primary research question of the present study is: Will implementation of the Dutch guideline improve pain reporting, pain measurement, and adequate pain therapy?

A RCT will be implemented, with clustering based on number of beds and number of medical oncologists to increase comparability of hospitals and to reduce contamination [64]. Differences of the effectiveness of the intervention between subgroups are expected. Factors that may predict inadequate cancer pain treatment include gender, race, low education, a better physical condition without metastatic disease, and age [65]. This paper describes the aims and methods of an RCT to evaluate on effectiveness of implementation of the Dutch guideline to improve pain reporting, pain measurement, and adequate pain therapy. The results of this study will be published in several scientific papers.

## Methods/design

### Objectives/hypothesis

The primary objective of this RCT is to reduce pain intensity of patients with cancer. The secondary objectives are to improve knowledge of the guideline of oncologists, nurses, and general practitioners (GPs) to increase pain reporting by patients and professionals, to increase systematic pain measurement by medical specialists and nurses working at oncology outpatient clinics, and increase quality of life of patients.

It is hypothesized that this innovative implementation strategy--which includes use of technical tools, training of professionals, and patient involvement--may increase the use of the guideline for pain management in cancer patients, and consequently reduce pain intensity (individual level and cluster level) and increase pain management. SMS-IVR alerts may serve as a tool to support self-management of patients.

### Time frame

This study will be conducted from 2011 to 2015.

### Study design

A non-blinded cluster RCT, will be performed in six oncology outpatient clinics of hospitals in the Southeastern region of the Netherlands, with hospital as cluster. Stratified randomisation will be performed based on pairs of two comparable hospitals regarding number of beds and number of medical oncologists. For each pair, one hospital will be randomly allocated to the intervention condition and the other to the control condition. Allocation to the intervention or control condition will be done before start of the intervention period by asking a statistician to select three closed envelopes (Figure 1). The allocation was generated by an independent statistician. Chosen implementation strategies are:

**Figure 1 F1:**
[figure not shown]
**Flowchart cluster randomisation of clinics**. Figure 1 shows the cluster randomisation of clinics. A cluster RCT with two arms will be performed in six oncology outpatient clinics of hospitals, with three hospitals in the intervention and three in the control condition. Clusters of hospitals will be determined based on number of beds and number of medical oncologists. We require 35 patients per hospital, a total of 210 patients.

1. Training of oncologists and nurses involved in cancer care on the most important aspect of the CPG comprising of three one-hour sessions, one main session at baseline, session two at month six, and the final session at month twelve (intervention arm).

2. Patients will receive SMS-IVR and personal advice by phone on how to reduce their pain if their pain rating is 5 or higher on a numeric rating scale (NRS) of 0 (no pain at all) to 10 (worst pain you can imagine) (intervention arm).

3. Patients will receive a leaflet on cancer pain of the Dutch Cancer Society (in both arms).

4. Oncologists and nurses will receive a leaflet for professionals on pain treatment of the Comprehensive Cancer Centre organisation (VIKC) (both arms).

5. GPs in the Netherlands will be offered a web-based training on the most important aspects of the CPG (intervention arm).

Follow-up measurements in all hospitals will be conducted to study the long-term effect of the intervention. Regarding the patients recruited in this study, the intention to treat principle will be used (Figure 2).

**Figure 2 F2:**
[figure not shown]
**Overall time chart of the study and per patient (M = month)**. Figure 2 shows the overall time-chart of the study and per patient. Each hospital has a period of twelve months to include 35 patients in the study. The total intervention period of hospitals is fifteen months (per patient twelve weeks). The first follow-up period is six months after the intervention period (M15) and the second, twelve months after the intervention period (M27). Each patient will be included in the study for 15 months.

Furthermore, four times, during a period of one week, transversal measurements will be performed in outpatient clinics of all six hospitals. Pain intensity of all patients who visit the oncology outpatient clinic during that week will be measured (See additional file 1).

### Participant recruitment and inclusion and exclusion criteria

To recruit hospitals, a letter was sent to hospital boards. If the board was willing to cooperate, a meeting with the oncologists and nurse practitioners in oncology was arranged to introduce the study. All hospitals are recruited from the Southeastern region of the Netherlands. Via the hospital boards, professional caregivers, oncologists, and nurses involved in cancer care of the six participating hospitals will be invited to take part. Patients who visit the oncology outpatient clinic will be screened for possible inclusion. Patients will be invited to take part by their medical oncologist or research nurse if they start to experience cancer-related pain.

Overall inclusion criteria for patients are: Diagnosed with cancer; aged 18 years or older; pain intensity of 3 or more on an NRS for the worst pain experienced in the last 24 hours; and having and being familiar with the use of a mobile phone.

Overall exclusion criteria are: Dementia and other severe cognitive disorders; no informed consent; and non-Dutch speaking or writing.

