### Intervention

The intervention was based on a pilot study with 13 patients, performed from November 2009 to January 2010, to test feasibility of SMS-IVR. The mean response rate was 62%. A significant reduction of highest pain intensity was found between pre- and post-test (p = 0.018). Pain fluctuated more in patients included in this pilot study than would be expected in patients who will be included in the present study, because only patients in palliative care were included in the pilot study.

Next, we developed a multifaceted intervention with hospital as cluster. Multifaceted interventions are proven to be more effective than single interventions [66,67]. Oncologists and nurses in the hospitals allocated to the intervention condition will be trained in-person, and GPs of patients that take part in the study will be offered a web-based training on the most important aspects of the CPG. Patients in the intervention condition will get SMS-IVR and will receive a personal advice by phone how to reduce their pain if their pain rating is 5 or higher on a NRS of 0 (no pain at all) to 10 (worst pain you can imagine). The research nurse of the hospital, specialised in pain treatment and trained for this project, will provide the personal advice.

The training for oncologists and nurses consists of three one-hour sessions, all given in-person; one main session at baseline, session two at six months, and the final session at 12 months. The first session will include the aim of the study, the main aspects of pain treatment in patients with cancer, pain measurement, and an instruction of the SMS-IVR system in detail. The next two sessions aim to summarise the first session and discuss problems associated with the implementation of the guideline.

Figure 3 shows the workflow of the SMS-IVR intervention. Patients receive SMS-IVR minimal once a week (Tuesdays), twice a day, during 12 weeks (Figure 2). SMS alerts are used as a reminder that they will receive an automatic telephone call 15 minutes later with IVR. SMS alerts will be received at 09:45 a.m. and at 2:45 p.m. At 10 a.m. and at 3 p.m. the patients will be called and invited to rate their pain on a scale of 0 (no pain) to 10 (worst pain imaginable). Morning: Rate your pain by choosing a number that best describes your WORST pain in the last 24 hours. Afternoon: Rate your pain at this moment.

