### Cluster randomisation of clinics

Clusters of hospitals will be determined based on number of beds and number of medical oncologists to increase comparability of hospitals and to reduce contamination [64]. Of each pair, one hospital will be randomly allocated to the intervention condition and the other to the control condition. Randomisation took place after all hospital boards and medical oncologists had agreed to participate. Next, an independent statistician allocated to the intervention or control condition based on clusters by selecting three closed envelopes (Figure 1). Patients will be invited to take part by their medical oncologist or research nurse.

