### Statistical analysis

To measure the effect of the implementation the PMI and NRS will be used and tested with general linear model analysis of variances (GLM ANOVA) repeated measures. Qualitative content analysis will be used to analyse the results of the focus group discussions and to analyse the interviews to evaluate the SMS alert intervention. Qualitative analysis will be supported by the use of the Atlas.ti software programme.

Data collected via SMS-IVR will be analysed for descriptive data: how did pain scores change and fluctuate in the whole period, what actions were taken by the research nurse, and did this intervention help the patients to manage pain? Subgroup analysis will be conducted. Differences in subgroups of the effectiveness of the intervention are expected. Subgroups will be classified by: age, gender, race, education, performance status, and classification of malignant tumors (TNM stage). The most recent version of SPSS will be used to perform the statistical analysis.

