In addition, our study will show possible barriers in SMS-IVR use for pain reporting in patients with cancer. This has never been done before. One of the possible barriers accounted for in the present study is asking too often about cancer pain and this could be experienced as confrontation with their disease. However, nothing is known yet about a proper frequency to ask patients about their pain. In the present study, patients will receive a weekly SMS alert twice a day. In the pilot study, patients received SMS alerts four times a week for four weeks. To achieve a similar response rate and compliance as was achieved in the pilot study, the frequency of SMS alerts has been reduced in the present study. It has been reduced to once a week if there is no pain and to maximal three times a week if pain remains present because the intervention period is three times as long. Asking patients about pain improves insight in pain intensity of professionals and it increases registration of pain [83,84]. Asking about pain in itself can reduce pain intensity [84]. Therefore, using SMS-IVR as a way to systematically measure pain is expected to reduce pain intensity.

Apart from the SMS-IVR, a pain dairy is necessary to obtain data on pain intensity in the control group and additional information in both control and intervention group. Asking about pain by measuring pain intensity with a pain diary in itself can reduce pain intensity [84]. Therefore, we expect that pain intensity difference between the intervention and the control group will be smaller. However, the possibility of earlier treatment is restricted to the intervention group. We expect an increase in motivation of patients to take part in the control condition and higher compliance during the study than without the pain dairy. However, because patients are expected to be more motivated to participate when SMS alerts are offered to them, this may cause selection bias. However, it was not possible to randomise at patient level, because of the multifaceted intervention. Oncologists and nurses should be trained before inclusion of patients.

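### Patients are recruited after allocation by unblinded staff, trained in pain measurement in one arm only, and the stated analysis makes weak use of the baseline data that could limit the resulting imbalance

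*Protocol article*

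**What the plan says.** **Order of events.** Study design describes the trial thus: "A non-blinded cluster RCT, will be performed in six oncology outpatient clinics of hospitals". It adds: "Allocation to the intervention or control condition will be done before start of the intervention period". Cluster randomisation of clinics gives the sequence: "Randomisation took place after all hospital boards and medical oncologists had agreed to participate". Patients come later, within a twelve-month window per hospital (Figure 2 legend).

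**Who recruits, and after what.** Under Participant recruitment: "Patients will be invited to take part by their medical oncologist or research nurse if they start to experience cancer-related pain". In the intervention arm the first training session covers, besides the study aim, "the main aspects of pain treatment in patients with cancer, pain measurement, and an instruction of the SMS-IVR system in detail" (Intervention), and the Discussion is explicit on timing: "Oncologists and nurses should be trained before inclusion of patients". More systematic pain measurement by these staff is itself a secondary objective (Objectives/hypothesis).

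**What the article concedes.** The Discussion says that "because patients are expected to be more motivated to participate when SMS alerts are offered to them, this may cause selection bias". It states that randomising patients was not possible, and expects the diary to raise motivation in the control condition.

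**Analysis.** PMI and NRS will be "tested with general linear model analysis of variances (GLM ANOVA) repeated measures" (Statistical analysis). Age, gender, race, education, performance status and TNM stage appear there only as subgroup factors. Table 1 schedules PMI at M0, M3, M9 and M15, and NRS from M0 to M3 and at M9 and M15.

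**The concern.** In a cluster trial, randomising hospitals protects the comparison of hospitals. It protects the comparison of patients only if patients are identified in the same way in both arms. Here the recruiters know the arm, and in one arm they have been trained on the attribute that makes a patient eligible. The Background says that professionals do not ask about pain systematically and that patients are reluctant to report it, so there is room for training to change who is found. The article also expects willingness to join to differ by arm. Three hospitals per arm are too few for chance to even out such differences.

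At stake are the second primary outcome, which uses SMS and diary scores that only recruited patients supply, and PMI as measured on the recruited cohort's follow-up schedule. A difference in who was enrolled could be read as an effect of the strategy, or could hide one.

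**Working it through.** **Benchmark.** The article plans for negative PMI to fall from 42% to 20%, with alpha 0.015 and 80% power. With unpooled variances and a two-sided test:

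n = (2.432 + 0.842)² × (0.42×0.58 + 0.20×0.80) / 0.22² = 10.72 × 0.4036 / 0.0484 = 89.4, so 90 per condition.

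This matches the stated figure, before any inflation for clustering. The planned effect is therefore 22 percentage points. The article gives no target effect or SD for NRS.

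**NRS illustration.** Everything here is assumed: no true effect, equal SD at entry and follow-up, entry pain lower by b = 1.0 point in the intervention arm, and correlation r between entry and each later measurement of 0.3, 0.5 or 0.7. The expected later difference is r × b.

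| Contrast | Formula | r = 0.3 | r = 0.5 | r = 0.7 |
|---|---|---|---|---|
| Post-treatment only, unadjusted | r×b | 0.30 | 0.50 | 0.70 |
| Arm main effect over M0, M3, M9, M15 | (b + 3rb)/4 | 0.475 | 0.625 | 0.775 |
| Change, or arm-by-time | −(1−r)×b | −0.70 | −0.50 | −0.30 |
| Post-treatment with M0 as covariate | rb − rb | 0 | 0 | 0 |

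Positive values favour the intervention. All entries halve if b = 0.5. The first two rows and the third have opposite signs: one recruitment imbalance helps or harms the intervention depending on a contrast that the article does not name.

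**The other case.** If the imbalance does not regress but stays at b throughout, the arm main effect is off by b, the change contrast by 0, and the M0-adjusted comparison by b − r×b = (1−r)×b, which is 0.70 to 0.30. The M0 covariate therefore removes the part of the imbalance that regresses to the mean. A lasting difference has to be captured by prognostic covariates, and what is unmeasured remains.

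**PMI illustration.** Also assumed: no true effect; two equal case-mix strata in control averaging 42% negative; the share of the stratum with fewer negative scores is higher by 0.10 to 0.30 in the intervention arm; post-treatment comparison only. Spurious difference = shift in share × gap between strata. The rejection rates use 90 per arm and design effect 1 + 29×0.015 = 1.435, so 90/1.435 = 62.7 effective patients per arm.

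| Strata (% negative) | Spurious difference | Share of 22 points | Rejection at alpha 0.015 |
|---|---|---|---|
| 32 / 52 | 2 to 6 points | 9% to 27% | 1.8% to 4.2% |
| 22 / 62 | 4 to 12 points | 18% to 55% | 2.6% to 15% |
| 12 / 72 | 6 to 18 points | 27% to 82% | 4.2% to 40% |

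Which arm would hold more of the favourable stratum is unknown. By the article's definition PMI is analgesic level minus pain level. Newly detected mild pain without an analgesic scores 0 − 1 = −1, inadequate; severe pain on a strong opioid scores 3 − 3 = 0, adequate. Milder pain at entry does not imply fewer negative scores.

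**The case against.** The case on the other side is substantial.

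- **Baseline is in the model.** M0 can be a level of the repeated factor, and a stable entry difference cancels in an arm-by-time test. A reader might infer that the plan has no baseline adjustment at all; the article does not support that. What stands is that the contrast is not named, and that an imbalance which regresses to the mean does not cancel.
- **Direction.** A reader might infer that trained staff will enrol milder cases and so produce a false benefit. The working shows that the sign depends on the contrast for NRS and on analgesic use for PMI.
- **Screening.** It is also tempting to picture control staff waiting for complaints. The article says, without distinguishing arms, that clinic visitors are screened, with one threshold of NRS 3 or more. Differential detection is a plausible inference, not a stated fact. A shared floor still does not equalise the distribution above it.
- **The diary.** It is a real, if partial, answer to unequal willingness to join. It does not touch who is identified and invited.
- **Population.** The first primary outcome is worded for all clinic visitors, and four one-week surveys cover all visitors; selective invitation affects these less. But the surveys are described as measuring pain intensity, whereas PMI also needs analgesic data. Table 1 places PMI on the patient follow-up schedule, and the sample size counts recruited patients.
- **Covariates may be settled elsewhere.** An analysis plan not shown may list them, in which case that part of the fix is done. It could not repair enrolment, which is fixed here.

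**Conclusion.** The point holds as a risk to the recruited cohort. Recruitment after allocation, by staff who know the arm and in one arm have been trained in pain measurement, could make case mix differ between arms and bias the NRS and cohort PMI comparisons. The documents do not show that it will, nor in which direction. The stated analysis is a weak defence, because its result under imbalance depends on an unnamed contrast and it uses the prognostic factors only for subgroups.

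The sizes are illustrations. For NRS, 0.475 to 0.775 points one way or 0.30 to 0.70 the other rests on an assumed 1.0-point imbalance and correlations of 0.3 to 0.7. A figure of 0.25 to 0.5 points (r = 0.5, imbalance 0.5 to 1.0) applies only to an unadjusted post-treatment comparison. For PMI, 2 to 18 points rests on the assumed strata and shifts.

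**What to change.** 1. **Analysis.** For the recruited cohort, estimate the arm effect on post-baseline NRS and PMI with M0 worst pain as a covariate (and M0 PMI for the PMI outcome), plus age, gender, TNM stage and M0 Karnofsky score. Report the unadjusted result as sensitivity and name its contrast.
2. **Screening.** Within the screening already planned, use the same NRS item in both arms, and log eligible, invited and refused patients with their scores.
3. **Selection check.** Compare enrolled patients' pain with that of visitors in the one-week surveys at the same hospital, restricted to visitors at or above the entry threshold so that like is compared with like.

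**Cost.** The analysis needs only wording: pain, PMI and Karnofsky are in Table 1, and age, gender and TNM stage are listed under Additional data. Under the planned rates there are about 0.42×90 + 0.20×90 = 37.8 + 18, or 56, negative PMIs, so TNM stage should be grouped coarsely. The log is a small burden on clinic staff. M0 is measured after staff training, so adjustment may remove a small part of the training effect; the unadjusted result helps to judge this. Adjustment cannot remove selection on unmeasured factors, which is why uniform screening and the log are needed as well.
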